**Strength**			
	Imagination/journey	Mediterranean cruise – aquafitness on the deck of the ship	Circus – task after tightrope dance
	Starting position	Seated, arms stretched above head	Standing upright behind chair, arms stretched above head
	Motor task	Lateral flexion with pool noodle	Lateral flexion with rope
	Sets and repetitions	3 sets with 2 repetitions for each side	2 sets with 3 repetitions for each side
	Muscle activity	Upper limbs and core	Upper limbs, core, and lower limbs
	Cognitive task	No additional cognitive task	Answering questions about circus performances (eg, Have you ever been to a circus? If yes: Which was the best circus act? If no: What do you think would be the most interesting thing if you visited a circus?)
**Balance**			
	Imagination/journey	Safari in Namibia – washing an elephant	World trip – washing an elephant
	Starting position	Seated, 1 arm is horizontally stretched, flexion in hip joint to shift body weight forward	Standing upright behind chair, one arm is horizontally stretched, flexion in hip joint to shift body weight forward
	Motor task	Slow and large arm movements in horizontal plane holding a small sandbag while leaning to left and right sides	Slow and large arm movements in horizontal plane holding a small sandbag while leaning to left and right sides
	Cognitive task	Answering questions about elephants (eg, Have you ever seen an elephant? Are there different kinds of elephants? What are the differences?)	Counting to 180 in steps of 6 (change hands at 90)
	Duration/repetitions	1 minute/approximately 10 repetitions per side	Approximately 1:30 minutes/15 repetitions per side
**Endurance**			
	Imagination/journey	Soccer World Cup – walking to the soccer training	On a treasure island – walking downhill through the jungle
	Starting position	Seated	Standing upright behind chair
	Motor task	“Walking” in seated position – lifting legs with active use of arms	“Walking” on the spot – lifting legs with active use of arms (if possible)
	Duration	1 minute	3 minutes
	Cognitive task	Answering questions about soccer and its rules (eg, Who knows some soccer rules? Do you know how many referees there are during a game?)	Naming animals living in the jungle. If a participant repeats an animal he or she is asked to name another one
**Flexibility**			
	Imagination/journey	Safari in Namibia – wood chopping for a campfire	Olympic Games – laola wave of the audience
	Starting position	Seated	Standing upright behind chair
	Motor task	Extention and flexion of the trunk, bringing arms in extention with maximal personal range of motion	Extention and flexion of the trunk, bringing arms in extention with maximal personal range of motion (try to increase range of motion)
	Set and repetitions/duration	3 sets with 10 repetitions (5 repetitions slow, 5 repetitions fast)	No repetitions defined, duration 3 minutes
	Cognitive task (example)	Performing in the same rhythm synchronous with other participants, 5 slow hits, 5 faster hits	Learning 3 different signals: 1= moving fast, 2= moving slow, 3= change direction of laola wave, performing according to signals

The departure takes about 5 minutes and aims to cool down and relax the body while leading participants out of imagination and back into reality. Similarly to the arrival, instructors guide participants through fixed sequences.

The MEP takes place twice a week on nonconsecutive days over a period of 16 weeks. Each session lasts 60 minutes with motor and cognitive tasks taking about 45 minutes to ensure sufficient time for rests and explanations. Prior to the first session, a social gathering session is held aiming for an initial familiarization and information acquisition with regard to participants and care facilities. Attendance and adherence of participants will be documented by instructors for each session. Adherence will be assessed using a short formula to rate attention, participation, motivation, and behavior of each participant.

Conventional treatment comprising, for instance, medication, care, or therapeutic applications is individually tailored and will be continued in all included participants of CG as well as IG.

**Figure 2 figure2:**
[figure not shown]
Distribution of motor qualities within the main parts of the multimodal exercise program.

### Outcomes

#### Determination of Outcomes

Primary outcomes refer to the motor qualities balance, mobility, and gait. Secondary outcomes are other motor variables such as strength and function of lower limbs and ADL as well as cognitive variables assessing overall cognition, language, processing speed, learning and memory, and visual spatial cognition. All outcome parameters are listed in Table 2. The aim of this study is to investigate changes in outcomes between IG and CG. Furthermore, the focus is on differences in all outcome variables between baseline and 16-week postassessment.

**Table 2 table2:** Primary and secondary outcome parameters.

	Outcome	Assessments (at baseline and 16-week postassessment)
**Primary outcomes**		
	Balance	Frailty and Injuries: Cooperative Studies of Intervention Techniques 4 (FICSIT-4) [51]
	Mobility	
		Timed Up and Go test [52]
		6-meter walk test [53]
	Gait	Gait analysis using GAITRite: temporal and spatial gait parameters (gait speed, cadence, cycle time, step length, step width, gait variability, single support, and double support)
		- Walking with normal speed
		- Walking with normal speed and the task counting backwards from 50
		- Walking with normal speed and the task naming animals
**Secondary outcomes**		
	Lower limb strength	Modified 30-second chair-stand test [54,55]
	Lower limb function	Short physical performance battery [56]
	Activities of daily living	
		Barthel Index (German version according to Hamburger Einstufungsmanual [57,58])
		Erlangen Test of Activities of Daily Living (E-ADL-Test) [59]
		7-item physical performance test [60]
	Overall cognition	Mini-Mental State Examination (MMSE) [45]
	Language	
		Verbal fluency “category animals”
		Phonemic fluency “S-words”
	Processing speed	Trail Making Test A [61,62]
	Learning and memory	
		California Verbal Learning Test, short version 1 [63]
		Digit span forward and backward [64]
	Visual spatial cognition	Clock drawing test [65]

The primary and secondary outcomes have been discussed in an international expert panel consisting of 14 scientists from 7 institutions in 3 countries (Germany, Australia, and Netherlands) with the disciplines sports science (especially focusing on locomotion research, sports therapy, kinesiology, biomechanics, training science, physical education and health, diagnostics, evaluation, and sports psychology), geriatrics/gerontology, psychology, and physiology. Among these experts, a standardized testing procedure has been determined focusing on relevance of outcomes as well as validity, reliability, objectivity, and feasibility of recording methods. The selected outcomes and recording methods are common in geriatric assessments and have been frequently used in previous studies examining IWD. However, it must be pointed out that most of recording methods regarding the motor qualities have not been developed for IWD. Feasibility of the test battery and recording procedure was tested in a sample of 20 participants prior to the current study. This pilot study proved feasibility of planned assessments in IWD.

Trained investigators with experience in sports science guide the baseline and postassessments in the care facilities. Prior to assessments, investigators participate in a special course to get detailed information about testing procedure and measurements. To standardize testing procedure and ensure comparability, a detailed testing manual is provided to which investigators are urged to strictly adhere. Accordingly, a detailed description of performing each assessment is given in Multimedia Appendix 2. Moreover, investigators will be educated about specific aspects of working with IWD.

#### Primary Outcomes

Static balance will be determined using the Frailty and Injuries: Cooperative Studies of Intervention Techniques 4 scale (FICSIT-4) [51]. Mobility will be assessed using the timed Up and Go test [52] and 6-meter walk test [53]. The 6-meter walk test aims to capture normal gait speed. To reduce bias caused by the testing situation, participants are not explicitly informed about time keeping.

Temporal and spatial gait parameters will be analyzed using the electronic gait analysis system GAITRite (CIR Systems Inc, Franklin, NJ) with an active length of 4.88 meters, a spatial resolution of 1.27 centimeters, and a scan rate of 120 hertz. The following parameters are of special interest: gait speed, cadence, cycle time, step length, step width, gait variability, single support, and double support (as percentage of cycle time). Gait parameters are recorded for 3 different conditions: walking with normal speed, walking with normal speed and the task of counting backwards from 50, and walking with normal speed and the task of naming animals.

Changes in gait parameters caused by dual task will be calculated using the equation seen in Figure 3. The generated value represents dual-task costs indicating the better performance under dual-task condition the lower this value is [66,67].

**Figure 3 figure3:**

Calculation of changes in gait parameters caused by dual task.

#### Secondary Outcomes

Strength of lower limbs will be determined by modified 30-second chair-stand test. In this modified version participants are allowed to use their arms [54,55], and the time to perform 5 repetitions is additionally measured. After a rest, fit participants complete a second trial without using arms with the same recording procedure as for the modified 30-second chair-stand test (including time for 5 repetitions). Function of lower limbs will be evaluated using the short physical performance battery, consisting of standing balance (Romberg, semitandem, tandem), gait speed, and 5 times sit-to-stand without using arms [56].

ADL will be determined using the Barthel Index (German version according to Hamburger Einstufungsmanual [57,58]), Erlangen Test of Activities of Daily Living (E-ADL-Test) [59], and 7-item physical performance test [60]. The Barthel Index will be completed by employees of the care facilities. To ensure standardized answers, employees receive a manual with detailed information. The E-ADL-Test and the 7-item physical performance test aim to practically examine ADL. Although the revalidation of the E-ADL-Test [59,68] showed that the tasks are too easy for mild dementia, for our target sample this test is considered as appropriate substantiated by the development for IWD. Furthermore, the E-ADL-Test is regarded as a valid and reliable instrument for assessing ADL of individuals with moderate to severe dementia [59,68].

Cognitive outcomes will be assessed using some subtests of the neuropsychological test battery Consortium to Establish a Registry for Alzheimer's Disease–Plus (CERAD-Plus) [69]. Overall cognition will be determined using MMSE [45]. Language will be examined regarding verbal fluency “category animals” and phonemic fluency “S-words.” The first fluency task provides information about verbal rate and fluency, semantic memory, language, executive function, and cognitive flexibility [70,71]. The second task examines fluency in a more strategic manner rather than the semantic memory. Processing speed and visual scanning will be determined using the Trail Making Test A [61,62]. In addition to CERAD-Plus, the California Verbal Learning Test, short version 1 (except forced choice recognition) [63], and digit span forward and backward [64] will be performed to assess learning and memory. Visual spatial cognition will be assessed using the clock drawing test [65].

Moreover, body mass and height will be measured using a Seca 813 Robusta scale and Seca 213 stadiometer (Seca, Hamburg, Germany) with an accuracy of 0.1 kilogram and 0.1 centimeter, respectively.

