### Intervention

The intervention is specifically developed for this study based on theoretical considerations, results of a pilot study [47], and a literature review [48]. The combination of motor and cognitive tasks used in the MEP aims to enhance the effectiveness of physical activity on cognition. This is theoretically supported by findings in healthy older adults showing that the combination of both yields larger effects on cognition than using each alone [49]. The pilot study (n=19) aimed to prove feasibility of the intervention and allowed first insights regarding the effectiveness. After a 10-week intervention, IG showed no significant changes in Alzheimer Disease Assessment Scale–Cognitive Subscale (ADAS-Cog, German version) [50] sum score but significant improvements in subscore orientation/praxis. In contrast, we found a significant decline in ADAS-Cog sum score of CG [47]. Moreover, IG showed significant improvements in get-up-and-go test whereas CG did not significantly improve (unpublished results). The literature review aimed at giving recommendations for designing interventions for IWD. Analyzed studies showed that a physical activity intervention for IWD should at least last 4 months with 2 to 3 sessions of 45 to 60 minutes per week. Moreover, interventions focusing on several motor skills (eg, endurance, strength, balance) seemed to be more effective than interventions with only 1 task [48]. Hence, the 10-week intervention of the pilot study has been revised for the current study. The revision, which aimed to provide a balanced MEP with specific, adequate, and intensity-demanding tasks, comprises adjustments of contents (motor qualities as well as connection between motor and cognitive tasks) and intervention duration (extension to 16 weeks).

The MEP will be guided by 2 skilled instructors with experience in sports science and performed as group training mainly in a seated position. A group will consist of a maximum of 12 participants and will be joined by familiar caregivers to support the instructors if needed. The underlying didactic concept focuses on specific needs and characteristics of IWD and includes increased supervision realized by 2 instructors, adaptation to the cognitive level of participants, adjusted communication (eg, simple language, nonverbal aspects), ritualization to give orientation and familiarity, and adequate complexity by simple and well-structured cognitive and motor tasks.

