### Dropout

We assume 3 reasons for dropout: (1) withdrawal from the study, (2) missing data, and (3) low attendance or adherence to MEP. Possible reasons for withdrawal are death, hospitalization, serious deterioration in state of health, refusal to participate, etc. Based on the literature review of Blankevoort et al [22], a dropout rate of 20% caused by withdrawal is expected. Missing data occur if participants are not able to complete the entire test battery because of motivational aspects or multiple motor and cognitive impairments. In addition, some participants will not participate at all in postassessments because of illness or other appointments. We assume a missing data rate of 15%. A total target number of 200 participants (100 per group) for the analysis and an assumed dropout rate (withdrawal and missing data) of 35% requires enrolling 270 participants into the study. Unfortunately, attendance and adherence are often not stated in previous studies [26]. Hence, we decided to double the sample of IG to ensure the required sample of 100 participants in this group. Low attendance and adherence may be caused by illness, motivation, other appointments, disinterest, or other reasons. Hence, a total sample size of 405 participants is required.

All participants will be asked at least twice if they are willing to participate in the assessments to reduce missing data. A familiar caregiver is asked to invite the participant if appropriate. If participants are not willing to complete all measures they are offered to choose assessments they are willing to complete. Moreover, all possible participants will be included in the data collection regardless of whether they discontinued or deviate from the intervention protocol. Caregivers will be asked to support the participants to get to training sessions to improve attendance. If participants miss a session, they are personally invited to the next training session.

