### Blinding and Pseudonymization

Investigators will be blinded to allocation wherever possible. It is not possible to blind participants or employees of care facilities regarding group allocation.

All data is stored in a strictly pseudonymous form. This is achieved by separating personally identifiable information of participants from data collected during baseline and postassessments. Collation of data is only possible with considerable effort at any time of the study. Thus, individual confidentiality will be ensured before, during, and after the study. Only selected team members have access to coded data.

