### Challenges

There are several challenges in performing intervention studies in IWD. These are related to the selected study design as well as its target group and thus cannot be avoided. However, it is important to deal with these challenges to minimize their impact.

A big challenge in performing intervention studies with IWD is maintaining blinding to group allocation. Although all investigators will be blinded to group allocation, there is a potential risk that participants will disclose their group allocation during assessments. To minimize this risk, investigators will be asked not to talk about the intervention during assessments.

Working with IWD entails several general challenges as they are often suffering from frailty and multimorbidity. According to different motor and cognitive impairments in IWD, it is not possible to develop an intervention completely suitable for all participants. Hence, some adaptions of the intervention cannot be avoided. However, instructors are asked to minimize such adaptions and adhere to the manual as strictly as possible. Besides this, IWD are vulnerable in relation to attendance, adherence, and missing data. For instance, multiple motor and cognitive impairments partially prevent IWD from participating in all subassessments. Thus, attempts to enhance attendance and adherence as personal communication, support, or repeated invitation are planned.

Further challenges are seen in cooperation with care facilities. Employees assume important responsibilities, such as suggesting potential participants, assessing ADL and state of health, or supporting assessments and intervention. Restricted time or missing expertise is a potential risk for limitations. To reduce such limitations, employees will be provided detailed information on how to report required data and support for further problems.

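### The Barthel Index, one of three ADL instruments, is rated by care-facility staff who cannot be blinded, so a benefit on it alone could reflect rater expectation

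*Protocol article*

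**What the plan says.** Table 2 lists three instruments for ADL, a secondary outcome: the Barthel Index, the E-ADL-Test and the 7-item physical performance test, each at baseline and at 16 weeks. On the first, Secondary Outcomes says: "The Barthel Index will be completed by employees of the care facilities". The accompanying safeguard is: "To ensure standardized answers, employees receive a manual with detailed information". The other two are described as practical examinations, and Determination of Outcomes has trained investigators guide the assessments.

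On blinding, the section Blinding and Pseudonymization says of investigators: "Investigators will be blinded to allocation wherever possible". Of the staff it says: "It is not possible to blind participants or employees of care facilities regarding group allocation".

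On the staff's part in the programme, Intervention says that each training group "will be joined by familiar caregivers to support the instructors if needed", and Dropout adds: "Caregivers will be asked to support the participants to get to training sessions to improve attendance". Challenges lists among the employees' responsibilities "assessing ADL and state of health, or supporting assessments and intervention".

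**The concern.** Employees complete the Barthel form at 16 weeks knowing who attended the exercise programme, and the staff group that supplies the raters also helps to run it. If that knowledge makes ratings kinder in one arm, the difference enters the comparison of change between groups, which is what the two-factor repeated-measures ANOVA tests. Randomisation does not protect against this, because the error arises after allocation. A larger sample does not protect against it either, because a fixed shift becomes easier to detect as numbers grow.

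At stake is a statement that the programme improves ADL, resting on a rating that could move without any change in the participant. The mediator and moderator analyses planned for ADL would carry the same error wherever they use the Barthel score.

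The article does not name this risk. Challenges discusses participants disclosing their group to investigators, and for employees only limited time and expertise.

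**Working it through.** **Step 1: does the text establish an unblinded rating?**

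| Question | What the article states | Section |
|---|---|---|
| Who rates? | Facility employees | Secondary Outcomes |
| Can they be blinded? | No | Blinding and Pseudonymization |
| Does the staff group support the programme? | Yes: caregivers join sessions and help with attendance; employees support the intervention | Intervention, Dropout, Challenges |
| Are both arms in the same facility? | Yes: subjects, not facilities, are randomised | Allocation |
| What is the safeguard? | A manual for uniform answers | Secondary Outcomes |

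The answer is yes for the Barthel Index and only for it.

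**Step 2: the plan's own figure.** Sample Size gives 200 analysed (100 per group) for the within-between interaction, with d = 0.2 (f = 0.1), two-sided alpha .05 and power .80. The correlation between measurements is not stated; 0.5 is assumed here. With two measurements, the noncentrality is f² × N × 2 / (1 − 0.5) = 0.01 × 200 × 2 / 0.5 = 8, which gives power 0.804. The figure of 200 is reproduced.

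**Step 3: what a rating shift would do.** Suppose there is no true effect, but allocation knowledge shifts the difference between arms by b standard deviations of change. The article gives no value for b, so a range is used. By the normal approximation,

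P(significant) = 1 − Φ(1.96 − b·s) + Φ(−1.96 − b·s), with s = 1/√(1/n₁ + 1/n₂).

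- At 100 and 100: s = 1/√0.02 = 7.07.
- At 270 and 135 (all 405 analysed at 2:1): s = √90 = 9.49.

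For b = 0.2 at 100 per group, b·s = 1.414, and 1 − Φ(0.546) + Φ(−3.374) = 0.293. The t-distribution gives 0.291.

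| Assumed shift b | 100 : 100 | 270 : 135 |
|---|---|---|
| 0 | 0.05 | 0.05 |
| 0.1 | 0.11 | 0.16 |
| 0.2 | 0.29 | 0.48 |
| 0.3 | 0.56 | 0.81 |
| 0.4 | 0.81 | 0.97 |

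**Step 4: scale.** At 100 per group the noncentrality for a shift b is b² × 50. Setting this equal to the plan's 8 gives b = 0.4, and the 0.81 in that row agrees with the planned power of .80. So, under the assumed correlation of 0.5, a shift of 0.2 SD of change is half the difference the trial is powered to find. It should not be equated with the plan's d = 0.2, which is on another scale.

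**The case against.** The other side has several good arguments, and most of them limit the point without removing it.

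- **The limitation is disclosed.** Secondary Outcomes and Blinding and Pseudonymization, read together, tell the reader that the rating is unblinded. This stands, but the article draws no consequence from it for how the Barthel result may be used.
- **Challenges does not claim full blinding.** A reader might take "Although all investigators will be blinded to group allocation" to mean that every outcome is assessed blind, and so see a contradiction. The sentence concerns investigators, a separate role from employees. The section is incomplete on this point, not false.
- **ADL has three instruments.** A reader might infer that any ADL benefit could come from rater expectation. That goes too far: two instruments are practical tests, and a benefit on the Barthel Index alone would stand out against them. ADL is also secondary, partly because the authors regard it as less objective to measure.
- **The same person need not rate and assist.** The text shows overlap of the staff group, not of individuals. The employee manual and the assessment appendix are not shown and may settle who rates.
- **Timing is inferred.** It is tempting to say that the baseline rating always precedes allocation, so that expectation enters only the second rating. The Barthel Index is not a minimisation factor, and the article does not date its baseline rating relative to allocation. Rating before allocation is likely but not stated.
- **The probabilities rest on assumed shifts.** This is so: at 0.1 SD the figure is about 11%, and with no shift it is 5%.
- **A rater from outside the sessions is still an unblinded employee.** This also stands, so changing the rater can be only a partial remedy.

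**Conclusion.** The point holds for the Barthel Index. Its rater is unblinded by the article's own account, the rater's staff group supports the intervention, and the manual does not conceal allocation. A benefit confined to this instrument could not be told apart from rater expectation. The primary outcomes, and the two practical ADL tests given by investigators blinded wherever possible, are not affected by this route.

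The documents show that bias is possible; they do not show that it occurs, how large it would be or which arm it would favour. The false-positive probabilities of about 11%, 29% and 56% at 100 per group are illustrations under assumed shifts of 0.1, 0.2 and 0.3 SD of change, with no true effect. They are not estimates for this trial. The point is worth acting on because the plan as written lets the Barthel Index carry an ADL claim, while better-protected measures of the same outcome are already being collected.

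**What to change.** 1. **Table 2 and Secondary Outcomes:** state that the ADL conclusion rests on the E-ADL-Test and the 7-item physical performance test. Designate the Barthel Index a supportive, unblinded rating that cannot carry an ADL claim by itself. Apply the same rule to the mediator and moderator analyses on ADL.
2. **Challenges:** add the unblinded Barthel rating to the listed limitations.
3. **Choice of rater:** where existing staffing allows, and for participants not yet rated at baseline, have the same employee make both Barthel ratings, chosen from those who do not support the sessions. This reduces the bias but does not remove it. Enrollment began in May 2015, so baseline ratings already made should be left as they are.

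The first two items change wording only and need no new measurement, visit or participants. The third requires choosing a rater at each facility, where the article already names staff time as a constraint. The price overall is that the Barthel result carries less weight.
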